##### Safety variables

Safety variables for the trial are treatment-emergent adverse events (that is, events either not present at baseline or present at baseline but of increased severity) and any serious adverse event (SAE).

All variables are measured at visit 0 (baseline), visit 15 (end of treatment), and follow-up assessments, if not otherwise specified. Adverse events will be reported as cumulative percentages at the end of the trial by treatment group.

### Analysis

#### General statistical methodology

All the main analyses will be performed on the ITT or FAS population between the two randomized groups. Complementary analyses will be performed on the PP population. For the confirmatory analyses, the fixed sequential test method for adjustment for multiplicity will be applied started with primary analysis and followed by the secondary analyses as numbered above. All other analyses will be exploratory. For comparison between the two randomized groups, Fisher’s non-parametric permutation test will be used for continuous variables, Fisher’s exact test for dichotomous variables, Mantel-Haenszel chi-square test for ordered categorical variables, and Pearson chi-square test for non-ordered categorical variables. Adjusted analyses will be performed with analysis of covariance for continuous outcome variables and with logistic regression for dichotomous outcome variables.

The main results will be the mean differences with 95% CI between the two groups, effect sizes, and *p*-values. For analyses of changes within groups, Fisher’s non-parametric permutation test for paired observation will be used for continuous variables and the Sign test for dichotomous and ordered categorical variables. All correlations will be performed with Spearman’s correlation coefficient.

All statistical tests will be two sided and conducted at the 5% significance level. The distribution of continuous variables will be given as mean, SD, median, Q1, Q3, minimum, and maximum, and distribution of categorical variables will be given as numbers and percentages. All major changes from the statistical analysis plan will be specified by subdividing into before and after database lock and unblinding. Normality of the data will be assessed inspecting the histograms.

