#### Statistical interim analysis and stopping guidance

There are no planned interim analyses for efficacy and no planned interim assessment for futility. The monitor of the study will provide stopping guidance should the necessity arise due to adverse events. The trial will be stopped after 60 subjects have completed the study.

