##### Secondary outcome variables

The secondary efficacy variables are other measures related to PLP and are listed below. As we are following the theory of fixed sequential multiple testing, the variables will be tested in the order in which they appear in the list below. All the variables apart from the Patients’ Global Impression of Change are assessed as changes between baseline and the specified timepoint.
Patients’ Global Impression of Change measured at visit 15 (single score [1–7])PRI change between baseline and follow-up timepoints (1, 3, and 6 months)PRI defined as a dichotomous variable indicating whether the patient has experienced a clinically meaningful reduction in pain (achieved with a decrease 50% or more [28] of the PRI)From the Questionnaire for Phantom Limb Pain (Q-PLP):
Weighted Pain Distribution Index (range [1–5]): sum of the scores given to pain ratings during the day, weighted by the amount of time spent in the respective level of pain [16]PLP intensity (NRS, [0–10])

Outcomes will be evaluated as changes between baseline and end of treatment and baseline and follow-up timepoints, if not otherwise stated.

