##### Exploratory outcome variables

EuroQol-5D-5L total score (mean value of the score given to the 5 items, [1–5])Pain Catastrophizing Scale Short Form total score (sum of the individual scores [0–24])Pain Disability Index (sum of the scores given to each item [0–70])Patient Health Questionnaire total score (sum of the individual scores [0–6])Pain Self-Efficacy Questionnaire total score (sum of the individual scores [0–12])Health Care Climate Questionnaire (HCCQ) total score (sum of the individual scores)Expectations for Complementary and Alternative Medicine Treatments Short Form (EXPECT-SF) total scoreOpinion About Treatment (OAT), total score [3–18]From the Questionnaire for Phantom Limb Pain (Q-PLP):
PLP intensity on Present Pain Intensity (PPI) scale, categorical, 6 levelsTelescoping (1 most proximal–6 most distal)Pain locations (1 most proximal–6 most distal, multiple selection possible)Stump pain, NRS, [0–10]Medication consumption (improved or not)Pain interference with work, NRS, [0–10]Pain interference with daily life activities (NRS, [0–10])Pain interference with sleep, NRS, [0–10]Pain qualities from the McGill QuestionnairePain frequency (improved or not)Exponential decay model of trial-by-trial improvement

Outcomes will be evaluated as changes between baseline and end of treatment and baseline and follow-up timepoints, if not otherwise stated.

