#### Analysis of secondary outcome variables

All secondary outcome variables will be analyzed between the two randomized groups according to the statistical methods presented in the section general statistical methodology, both on the ITT population using stochastic imputation and on the PP population. Within-group comparison will also be performed on the ITT population.

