#### Analysis of exploratory outcomes

All exploratory outcome variables will be analyzed between the two randomized groups according to the statistical methods presented in the section general statistical methodology, on the ITT population using stochastic imputation. Within-group comparison will also be performed on the same population. Prosthetic usage data will be descriptively analyzed.

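### The within-group Sign test does not test no change for the 50% PRI responder, because that variable is already a change from baseline

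*SAP article*

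**What the plan says.** General statistical methodology sets tests by variable type. For within-group change it names Fisher's permutation test for paired observations for continuous variables and "the Sign test for dichotomous and ordered categorical variables". It adds: "All statistical tests will be two sided and conducted at the 5% significance level".

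Among the secondary outcomes is "PRI defined as a dichotomous variable indicating whether the patient has experienced a clinically meaningful reduction in pain", which is "achieved with a decrease 50% or more" of the PRI. The introduction to that list says that every variable except the Patients' Global Impression of Change is assessed as a change from baseline. The exploratory list adds two items from the Questionnaire for Phantom Limb Pain (Q-PLP), medication consumption and pain frequency, each labelled only as improved or not.

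The section on secondary outcomes states: "Within-group comparison will also be performed on the ITT population". The section on exploratory outcomes states: "Within-group comparison will also be performed on the same population". Neither exempts a variable.

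**The concern.** A Sign test asks whether, among patients who changed, shifts in the two directions are equally likely. It needs a paired difference that can go either way. The PRI responder flag cannot supply one. It is itself a comparison with baseline, so nobody has a value at visit 0, and a patient whose PRI is unchanged or higher is simply a non-responder. Worsening can never register as a minus sign.

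Followed literally, the SAP would therefore produce a within-arm p-value for the responder that does not answer whether the arm changed. Under one way of coding it, the 2:1 allocation also makes significance likelier in the PME arm than in the PMI arm at the same response rate. A reader could mistake that pattern for a treatment effect.

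**Working it through.** The SAP gives no figure for this test, so there is none to reproduce.

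**Inputs**
- Test: Sign test, two-sided, 5% (General statistical methodology).
- Arm sizes: "The trial will be stopped after 60 subjects have completed the study". At 2:1 this is 60 × 2/3 = 40 PME and 60 × 1/3 = 20 PMI.
- Response rates: not given. They are varied below as an assumption.

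**Reading A: baseline coded as non-responder for everyone.** Non-responders are ties and drop out, and each of the r responders is a plus sign. Hence p = 2 × 0.5^r.
- r = 5: 2 × 0.5^5 = 0.0625
- r = 6: 2 × 0.5^6 = 0.031
- r = 10: 2 × 0.5^10 = 0.002

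Arm size and the number who worsen do not enter the formula.

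**Reading B: responders against non-responders.** This is an exact binomial test of a 50% response rate.
- With 40 patients it rejects at 13 or fewer, or 27 or more, responders.
- 10 of 40 gives p = 0.002 and 4 of 20 gives p = 0.012, in both cases because fewer than half responded.
- If nobody responds, p = 1.8 × 10^-12 (n = 40) or 1.9 × 10^-6 (n = 20).

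**One example, n = 40: 10 improved, 10 worsened, 20 unchanged.** Reading A gives p = 0.002 and reading B gives p = 0.002. A Sign test of improved against worsened, ties dropped, compares 10 with 10 and gives p = 1.00.

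**Rejection rates when there is no net change.** Assume that a proportion p improves, the same proportion p worsens and the rest stay the same. Reading A rejects with probability P(X ≥ 6), X ~ Binomial(n, p). The last column is the Sign test of improved against worsened.

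| n | p | Reading A | Reading B | Improved v worsened |
|---|---|---|---|---|
| 40 | 0.05 | 1.4% | 100% | 0.5% |
| 40 | 0.10 | 20.6% | 100% | 1.9% |
| 40 | 0.20 | 83.9% | 98.1% | 2.9% |
| 40 | 0.30 | 99.1% | 70.3% | 2.9% |
| 40 | 0.50 | 100% | 3.8% | 3.8% |
| 20 | 0.10 | 1.1% | 98.9% | 0.5% |
| 20 | 0.20 | 19.6% | 80.4% | 1.9% |
| 20 | 0.30 | 58.4% | 41.6% | 2.4% |
| 20 | 0.50 | 97.9% | 4.1% | 4.1% |

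Reading A is below 5% only when very few patients improve. Reading B is near 5% only when half improve and half worsen. The improved-against-worsened test stays within 5% throughout.

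**Plausible chance response for the PRI.** The Sample size section gives a mean improvement of 5.75, a 51% relative improvement and an SD of 4.89. Taking the ratio as a baseline mean gives 5.75 / 0.51 = 11.3. Assume no mean change, normal changes with SD 4.89, whole scores from 0 to 45 and gamma-distributed baselines. The baseline SD is not given and is varied from 0 to 8. By simulation, 13.0% to 19.4% of patients then fall by half or more through fluctuation alone. Reading A rejects with probability 0.42 to 0.82 in 40 patients and 0.04 to 0.18 in 20.

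**The case against.** The assignment of tests is a generic rule by variable type, and it is sound for binary or ordered items observed twice. A reader might infer that every dichotomous outcome is affected. The SAP does not support that. Medication consumption and pain frequency come from the Q-PLP, which Table 8 schedules at visit 0, at every treatment visit and at follow-up. The section on prior and concomitant medications treats intake as both a baseline and an efficacy variable. Worsening can therefore be observed, and an improved-against-worsened Sign test is available. Pain locations, coded per site, would also be valid paired binary data. This objection stands and confines the definite fault to the PRI responder.

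It can also be said that within-group testing was never meant for variables without a paired value, since the Global Impression of Change has none either. This stands only in part. The secondary list names the Global Impression of Change as its one exception to assessment as change. It does not except the responder, and the methodology names dichotomous variables explicitly.

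A reader might further infer that confirmatory testing is compromised because the responder is in the fixed sequence. It is not. The Framework section sets superiority between treatment groups, and the between-arm test for a dichotomous outcome is Fisher's exact test, which is valid here. For the primary variable the SAP itself gives within-group changes lower evidence value. The sections on secondary and exploratory outcomes do not repeat that caution, and less weight would not correct a wrong null in any case.

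Finally, the 0.42 to 0.82 range rests on an unstated baseline SD and a rescaled result from another trial. That is fair. The six-responder threshold and the unstated 50% null need none of those assumptions.

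**Conclusion.** Wrong as written, and minor. For the PRI responder the planned within-group Sign test either counts only plus signs, so that any six responders are significant, or tests a 50% response rate that the SAP never states. Both follow from the definition of the variable. The rejection rates depend on assumed response rates: with 20% improving and 20% worsening, reading A rejects 84% of the time in 40 patients and 20% in 20.

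Medication consumption and pain frequency are affected only if the test is run on the collapsed label. The harm is limited to supportive within-arm p-values. No between-arm comparison, no step of the fixed sequence and no part of the primary analysis changes.

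**What to change.** Amend the within-group sentence in General statistical methodology to say three things:

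- The PRI responder is not tested within groups. Its proportion is reported per arm with an exact 95% CI. Within-arm change in PRI already has the paired permutation test.
- For medication consumption and pain frequency, the Sign test compares improved with worsened patients, and unchanged patients are dropped as ties.
- The Sign test stays for other ordered or binary items observed at both visits.

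Fisher's exact test between arms stays as planned. The cost is one sentence. No data, power or confirmatory test is lost; only an uninterpretable within-arm p-value goes.

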#### Analysis of the primary outcome variable

The main analyses will be performed using the ITT population and it will be unadjusted. The comparison of change in PRI between baseline (visit 0) and end of treatment (visit 15) between the two treatment groups will be carried out with a two-sided Fisher’s non-parametric permutation test on significance level 0.05. We chose to use a non-parametric test for the main analysis as it does not rely on the assumption that the data are normally distributed, which we cannot ensure a priori. Missing data will be imputed with stochastic imputation using 50 datasets; it should be noted that this method of imputation differs from the use of last observation carried forward (LOCF) proposed in our previous work [20], as advised by our senior statistician consultant and reviewers. The difference in change in PRI with 95% CI will be given together with effect size and *p*-value.

*The following sensitivity analyses will be performed for the primary analysis:*
The robustness of the estimate of treatment effect will be assessed by adjusting for the baseline characteristics used for randomization (level of PLP at baseline (NRS), baseline PRI, level of amputation). For adjusted comparison between two groups, the analysis of covariance (ANCOVA) will be used with intervention/control as the independent variable and the baseline characteristics used for randomization as covariates. The effect estimates will be presented as group difference with 95% confidence intervals. This analysis will be conducted on the ITT population using stochastic imputation to handle missing data.The impact of the imputation method will be assessed by running the same analysis as point 1 using LOCF for missing data imputation.The impact of missing data will be assessed by running the unadjusted comparison on the full analysis set (FAS) using the same statistical methods as in primary analyses without imputing missing data.

A complementary analysis on the primary variable will also be performed on the PP population.Changes within groups will also be performed but with lower evidence value.

#### Analysis of secondary outcome variables

All secondary outcome variables will be analyzed between the two randomized groups according to the statistical methods presented in the section general statistical methodology, both on the ITT population using stochastic imputation and on the PP population. Within-group comparison will also be performed on the ITT population.

#### Analysis of exploratory outcomes

All exploratory outcome variables will be analyzed between the two randomized groups according to the statistical methods presented in the section general statistical methodology, on the ITT population using stochastic imputation. Within-group comparison will also be performed on the same population. Prosthetic usage data will be descriptively analyzed.

#### Subgroup analysis

The effect on the primary outcome will be analyzed also in subpopulations defined by: level of amputation, cause of amputation and gender. Subgroup analyses will be carried out using the approach followed for the main unadjusted comparison.

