#### Randomization

Participants that meet the inclusion criteria (see protocol [20]) and signed the informed consent were assigned to the experimental or active control group in proportion 2:1, according to the optimal allocation scheme of minimization. Initial description and methods of minimization were introduced independently by Taves [21] in 1974 and Pocock and Simon [22] in 1975. In short, the minimization algorithm was chosen because it allows dynamic allocation of the subjects, in which each allocation is influenced by the current state of overall treatment balances. Specifically, the minimization schemes ensure that allocation balance is maintained by giving higher allocation probabilities to interventions selected in favor of reducing total imbalance. The randomization strategy was chosen to reduce the likelihood of baseline imbalance of potentially prognostic covariates between the two treatment groups and to maximize the amount of information collected on the experimental treatment. The following minimization factors were considered: level of amputation (upper and lower), baseline PLP based on the Numeric Rating Scale (NRS) (low 1–4 and high 5–10), and investigation site (eight centers). The minimization process is conducted using the opensource desktop application MinimPy [23] operated by the monitor of the clinical trial. Patients were randomized as they were enrolled. Specifically, a therapist at the investigation site was responsible for evaluating the eligibility of the subject by carrying out all the assessments included in visit 0. If the patient was deemed eligible, the therapist would assign a subject ID, which also identifies the investigation site, and communicate it to the monitor of the study together with information regarding the abovementioned minimization factors (level of amputation and the NRS value of PLP). The monitor would then input these values in the software and get as result the allocation group. The allocated treatment would then be communicated back to the therapist responsible for the treatment.

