### Statistical analysis principles

#### Confidence intervals and *p-*values

The main results will be presented as mean differences with 95% confidence intervals between the two groups together with effect sizes and *p*-values. All significance tests will be two-sided and conducted at the 5% level.

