***Background information***					
Age at randomization [years, mean (SD)]					
Sex [% male]					
Time since amputation [months, mean (SD)]					
Time since onset of PLP [months, mean (SD)]					
Reason of amputation	trauma				
	cardiovascular				
	cancer				
	other				
Type of prosthesis	none				
	active/myoelectric				
	cosmetic				
	passive				
	body-powered				
Daily prosthesis use [hours, mean (SD)]					
Minimization factors	Level of amputation	upper limb			
		lower limb			
	Intensity of PLP [NRS (0-10), mean(SD)]	high (> 4)			
		low (<= 4)			
	Investigational site	#1			
		#2			
		#3			
		#4			
		#5			
		#6			
		#7			
		#8			
		#9			
Chosen treatment frequency	once a week				
	twice a week				
	five times a week				

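### The subgroup plan repeats the main test within each subgroup and gives no interaction estimate, so it cannot show whether the PME effect differs between subgroups

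*SAP article*

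**What the plan says.** The section Subgroup analysis consists of two sentences. The first names the factors: "The effect on the primary outcome will be analyzed also in subpopulations defined by: level of amputation, cause of amputation and gender". The second gives the method: "Subgroup analyses will be carried out using the approach followed for the main unadjusted comparison".

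The approach it points to is in Analysis of the primary outcome variable. There the SAP says "The main analyses will be performed using the ITT population and it will be unadjusted", and the comparison of PRI change is a two-sided "non-parametric permutation test on significance level 0.05". The result is to be given as a difference with 95% CI, effect size and p-value. The section Confidence intervals and p-values adds: "All significance tests will be two-sided and conducted at the 5% level".

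The only model for the primary outcome is the sensitivity ANCOVA. It has covariates but no interaction term, and none appears elsewhere in the SAP.

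On status, Multiple comparisons and multiplicity confines confirmatory claims to the fixed test sequence. General statistical methodology says of everything outside that sequence: "All other analyses will be exploratory".

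The subgroup section does not list the levels of each factor. Randomization gives amputation level two levels. The baseline template (Table 3, row "Reason of amputation") gives four causes: trauma, cardiovascular, cancer and other.

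**The concern.** The purpose of a subgroup analysis is to ask whether the treatment effect varies with a patient characteristic. A separate test in each subgroup asks something else: whether the effect in that subgroup differs from zero. Two subgroups with the same true effect can easily fall on opposite sides of 5%, because each holds only part of the sample and the smaller part has less power.

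The trial has about 67 patients, of whom about 22 are controls, so the subgroups are small. The risk is a published remark that the treatment works after upper but not lower limb amputation (or the reverse) when the data show no such difference. If there is no effect at all, the risk is an isolated significant subgroup.

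**Working it through.** **Inputs from the SAP.** Difference 4, SD 4.89, 2:1 allocation, two-sided 5%, 60 evaluable patients (40 PME, 20 PMI), all from Sample size and Trial design.

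**Assumptions.** Gender has two levels. Cause has the four levels of Table 3. Subgroup shares are assumed throughout.

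**The plan's own figure.** The SAP gives no figure for subgroups; the nearest is the 60 patients for the main test. It is not reproduced exactly. A t-test calculation needs 19 + 38 = 57 (power 81.6%), and 20 + 40 gives 83.6%. So 60 is slightly conservative, and the gap does not bear on this point.

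**Number of tests.** 2 + 4 + 2 = up to 8. If they were independent, the chance of at least one false positive would be 1 − 0.95^8 = 33.7%. They share patients, so the true figure is lower (simulated below).

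**Power inside a subgroup.** With n controls and 2n treated, SE = 4.89 × √(1/n + 1/(2n)) and the noncentrality is 4/SE. For n = 10, SE = 4.89 × √0.15 = 1.894 and the noncentrality is 2.11. Noncentral t power:

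| PMI + PME | Power for a 4-point effect |
|---|---|
| 15 + 30 | 71.5% |
| 14 + 28 | 68.4% |
| 10 + 20 | 53.2% |
| 6 + 12 | 33.7% |
| 5 + 10 | 28.3% |
| 3 + 6 | 17.1% |

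**One two-level factor, same effect in both levels.** P(one significant, the other not) = a(1 − b) + b(1 − a), where a and b are the two powers:
- 50/50 split: 2 × 0.532 × 0.468 = 50%
- 70/30 split: 0.684 × 0.663 + 0.337 × 0.316 = 56%
- 75/25 split: 0.715 × 0.717 + 0.283 × 0.285 = 59%

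**All three factors, by simulation.** One set used 60 patients, t tests in place of permutation tests, 3,000 trials per scenario and three assumed mixes (one amputation level 30-50%, one gender 50-75%, trauma 55-70%). A second set used 67 patients (45 v 22), permutation tests and one mix (50/50, 75/25, cause 60/15/15/10), in runs of 1,500 and 800 trials. The true effect was the same in every subgroup.

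| True effect | At least one discordant factor, t tests | Same, permutation tests |
|---|---|---|
| 0 | 24-28% | 25% |
| 2 | 49-55% | 54% |
| 4 | 87-89% | 91-92% |

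With no effect, at least one subgroup test was significant in 25-28% of trials (t tests) and 23-25% (permutation tests). Leaving cause out, discordance in level or gender occurred in 16-17%, 40-42% and 69-76% of trials for true effects of 0, 2 and 4.

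**Sparse levels.** With, for example, 4 PME and 2 PMI patients there are 6!/(4!2!) = 15 allocations, so the smallest attainable p is 1/15 = 0.067. Such a test cannot reach 5% whatever the data show.

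**With interaction tests instead.** One test per factor, cause taken as trauma v other, gave at least one false signal in 13-15% of trials whatever the main effect (independence: 1 − 0.95³ = 14.3%). For a 50/50 factor with 60 patients, the interaction SE = 4.89 × √(2 × (1/10 + 1/20)) = 2.68. Power for a 4-point interaction is Φ(4/2.68 − 1.96) = 32%, and 80% power needs about 2.8 × 2.68 = 7.5 points.

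**The case against.** The best defence is that the SAP claims little for these analyses. They lie outside the fixed sequence and are exploratory, so no subgroup result can become confirmatory. The approach they inherit already yields a difference with 95% CI, so subgroup estimates with intervals are implied. Both points stand. They limit the harm, but an exploratory p-value is still reported, and the label does not turn a within-subgroup test into a comparison between subgroups.

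A reader might infer that the SAP will declare subgroups different by comparing which tests are significant. It does not say so. It sets no rule for judging differences, and the fault is one of omission.

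The figures also depend on assumptions. The SAP gives no subgroup shares, and the four causes come from a table template. Part of the 87-92% is mechanical: small cause groups have little power, so a significant trauma result is almost bound to have a non-significant neighbour. The figures without cause, and for a single factor, do not depend on this.

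Finally, an interaction test would miss most plausible heterogeneity at this size. That is true, and it is a reason to show the wide interval openly rather than leave readers to compare p-values.

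**Conclusion.** The point holds as a weakness of the stated method. Separate unadjusted tests, with no interaction estimate and no interpretive caution, cannot show whether the effect differs by amputation level, cause or gender. At the planned effect, a misleading split in one two-level factor is about as likely as not, or somewhat more (50-60%).

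A reader might conclude that spurious differences are almost certain. The evidence does not support that. Over all three factors the chance runs from about 24% to 92%. It nears the top only if the full 4-point effect exists and cause is kept in four levels. All these figures rest on assumed subgroup shares and a common SD of 4.89.

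The primary analysis and the confirmatory sequence are not affected. This should be corrected, but it does not threaten the trial's main conclusion.

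**What to change.** Amend Subgroup analysis as follows.
- For each factor, fit a model of PRI change with treatment, the factor and their interaction. Report the interaction estimate with 95% CI and p-value. If cause keeps more than two levels, give a joint test.
- Present the PME-PMI difference with 95% CI in each subgroup, for instance in a forest plot, and state that within-subgroup p-values are not evidence that effects differ.
- Fix, blind to outcome, how sparse cause categories will be pooled. The clean file meeting before database lock is a natural place to do this from baseline counts.
- Repeat in this section that the results are exploratory, and state the low interaction power: about 32% for a 4-point interaction in an evenly split factor with 60 patients.

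The cost is a few sentences and one extra model per factor, with no new data. The drawback is that the interaction intervals will be wide and most will settle nothing.
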